### Secondary outcomes

#### Cardiovascular risk change

The SCORE 2 charts will be used to calculate cardiovascular risk at T0, T2, and T3, allowing for the evaluation of changes in risk compared to baseline.

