The cardiovascular evaluation will include measurements of blood pressure, heart rate, objective examination and cardiovascular risk assessment using SCORE 2 charts, incorporating essential variables such as age, gender, systolic blood pressure, total cholesterol, HDL cholesterol, and smoking status (12). Blood analysis will also be conducted, assessing parameters such as total cholesterol, HDL and LDL cholesterol, triglycerides, high sensitivity C-Reactive Protein (CRP), glycated hemoglobin, and/or glycemia.

Participants in Groups B and D will also undergo a salivary swab for PRS analysis.

Subsequently, participants will have a disclosure visit (T1) after 1 month, a follow-up visit (T2) after 5 months, and a final follow-up visit (T3) at 12 months.

During the disclosure visit (T1), participants in all groups will receive an explanation of their lifestyle pattern and cardiovascular risk profile based on SCORE 2 charts, along with written preventive advice for risk reduction and lifestyle changes. Participants in the digital intervention groups (C, D) will also receive an app and a smart band to monitor various health data. A comprehensive demonstration during smart band delivery, along with written instructions on its usage, will be provided to ensure participants consistently utilize the smart band throughout the study, with the recommendation for daily application (24–26). Participants in the PRS groups (B, D) will receive the disclosure of their genetic CVD risk profile.

At both follow-up visits (T2, T3), the comprehensive questionnaire will be administered again to assess changes in lifestyles and psychological status. Any challenges with smart band usage will also be identified. At the final visit (T3), the cardiovascular risk profile will be recalculated, and participants will undergo a final full assessment, evaluation of the lifestyle category, and blood test to evaluate changes in cholesterol levels and other parameters.

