#### Lipid profile

Blood analysis will be conducted at T0 and T3 to measure changes in lipid levels compared to baseline. Parameters examined will include total cholesterol, HDL and LDL cholesterol, and triglycerides.

By assessing these measures at different time points throughout the trial, the study will evaluate the impact and progress achieved by participants over the course of the intervention.

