#### Statistical methods for primary and secondary outcomes

The primary analysis will be based on the intention-to-treat principle, where all randomized participants will be analyzed according to their allocated study arm. Baseline characteristics of the four arms will be summarized using descriptive statistics. The baseline characteristics of those who withdraw will be assessed against those who remain in the study.

Groups D, C, and B will be compared with group A to evaluate the marginal effect of adding at least one intervention or both. The analysis will employ adjusted mixed-effect models for repeated measures to assess significant differences in lifestyle patterns, lipid, and CVD risk profiles from baseline to the various follow-up time points (T).

Furthermore, an analysis of the primary outcome will be conducted in a per-protocol fashion to account for non-compliance with uptake of the CVD PRS or use of the app/smart band evaluated at T2 and T3, as well as missed appointments for the complete CVD risk result, as prescribed by their allocated intervention.

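### The CVD risk outcome is change in a value read from SCORE 2 charts: analysing chart cells would cost precision, and the T2 value has no current cholesterol behind it

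*Protocol article*

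**What the plan says.** In the protocol article, the section Cardiovascular risk change defines the outcome: "The SCORE 2 charts will be used to calculate cardiovascular risk at T0, T2, and T3". What is evaluated is each later value set against the one at T0. The Study procedure section describes the baseline evaluation as "cardiovascular risk assessment using SCORE 2 charts, incorporating essential variables such as age, gender, systolic blood pressure, total cholesterol, HDL cholesterol, and smoking status". The eligibility criteria also refer to the charts; the abstract's sentence on outcomes names SCORE 2 alone.

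The statistical methods section plans adjusted mixed-effect models for "significant differences in lifestyle patterns, lipid, and CVD risk profiles from baseline to the various follow-up time points", with groups B, C and D each compared with group A.

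On timing, the Study procedure section sets "a follow-up visit (T2) after 5 months, and a final follow-up visit (T3) at 12 months". For those visits it says "At both follow-up visits (T2, T3), the comprehensive questionnaire will be administered again to assess changes in lifestyles and psychological status", and then "At the final visit (T3), the cardiovascular risk profile will be recalculated", together with a full final assessment and a blood test. The Lipid profile section says "Blood analysis will be conducted at T0 and T3 to measure changes in lipid levels compared to baseline". No section says whether age is updated or held fixed when risk is recalculated.

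**The concern.** A chart gives one risk value for each cell, that is, for a range of values of each graded input. Participants enter with a 10-year risk between 2.5 and 10% and are followed for 12 months, so true changes will be small. Read from cells, many of them become zero, while a small change near a cell edge becomes a jump. The component values are collected at T0 and T3, so the precision is obtained and then thrown away.

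The outcome is listed as secondary, but the Objectives section makes CVD risk modification one of the two endpoints of the primary objective. The sample size was set on lifestyle transition, with LDL cholesterol checked as well. No power is stated for SCORE 2, so there is no known reserve to absorb an avoidable loss.

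**Working it through.** **Evaluable number.** 255 per group with 30% withdrawal gives 255 × 0.70 = 178.5. The protocol's own sample size is consistent with this number. For a four-group chi-square test (3 df) on 5, 8, 10 and 15%, the mean is 9.5% and the squared deviations sum to 0.0053. The noncentrality at n = 178 is 178 × 0.0053 / (0.095 × 0.905) = 10.97, and the power is 80.3% (80.5% at 179). The documents state no figure for SCORE 2, so everything below rests on assumptions.

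**Banding of one input.** Let w be the band width and s the SD of within-person change. Each rounded reading adds variance w²/12, so a change between two readings adds w²/6. Information kept = 1 / (1 + w²/(6s²)).
- w = s: 1 / (1 + 1/6) = 0.857, and 178 × 0.857 ≈ 153.
- w = 2s: 1 / (1 + 4/6) = 0.600, and 178 × 0.600 ≈ 107.

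A simulation of 400,000 draws gave 0.855 and 0.599.

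**Why this is noise and not bias.** Suppose systolic pressure falls by 5 mmHg and values are spread evenly within 20 mmHg bands. Then 1 − 5/20 = 75% show no change and 25% drop a whole band. The mean change is still 0.25 × 20 = 5 mmHg. With 10 mmHg bands, 50% show no change.

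**Ageing, if age is updated.** With age bands of b years, a fraction 1/b crosses a band by T3 and (5/12)/b by T2. For b = 5 this is 20% and 8.3%; for b = 10 it is 10% and 4.2%.

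**Composite score.** A generic log-linear risk was simulated with 178 per arm and 2,000 replicates. The assumptions were:
- bands of 5 years, 20 mmHg and 1 mmol/L, with banded risk rounded to a whole percent;
- SD of change 12 mmHg and 0.6 mmol/L; true effect −4 mmHg and −0.1 mmol/L;
- coefficients 0.014 per mmHg and 0.15 per mmol/L, and 0.05, 0.07 or 0.09 per year of age.

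| Age coefficient | Continuous, age advancing | Continuous, age fixed | Banded, age advancing | Banded, age fixed |
|---|---|---|---|---|
| 0.05 | 89.8% | 89.8% | 63.3% | 71.6% |
| 0.07 | 87.7% | 88.1% | 54.0% | 70.0% |
| 0.09 | 84.3% | 85.4% | 47.8% | 69.7% |

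Entries are power for one arm against control.
- Banding with age fixed costs about 16 to 18 points (85.4 − 69.7 and 89.8 − 71.6).
- Advancing age costs a further 8 to 22 points when risk is banded (71.6 − 63.3 and 69.7 − 47.8), but only about 1 point or less when it is continuous.
- Mean change in the control arm is about +0.4 to +0.8 points with age advancing and about +0.1 with age fixed.
- The difference between arms is −0.37 to −0.46 points over all twelve cells, and close to the same across the four versions at each age coefficient.

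The two calculations agree. Here w/s = 20/12 = 1.67, so the formula gives 1 / (1 + 2.78/6) = 0.68. With age fixed and coefficient 0.05, the simulated SDs of change give 1.116² / 1.359² = 0.67.

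**Inputs by visit.** The outcome section calls for risk at T0, T2 and T3. Total and HDL cholesterol are SCORE 2 inputs. Blood is taken at T0 and T3 only, and the Study procedure section mentions recalculated risk only at T3. At T2 there is no current cholesterol to enter, whether into a chart or an equation.

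**The case against.** The strongest objection is that the word charts may be loose. The article speaks of calculating and recalculating risk, and the abstract says only SCORE 2. The derivation of the analysed value may be settled in an analysis plan that is not shown. This stands in part: if a continuous score is meant, one sentence closes the point. But the outcome definition names the charts as the means of calculation, and nothing elsewhere in the article replaces them.

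It can also be said that the documents give neither band widths nor coefficients. That stands fully for the size of the loss. The direction follows from reading a graded table in place of the recorded values.

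Three stronger readings are tempting and are not supported.
- A reader might infer that ageing distorts the treatment comparison. It does not: allocation is randomized and each intervention group is compared with a concurrent group A, so the same ageing applies to all.
- A reader might infer that the plan lets age move forward. The article lists age as an input and is silent on whether it is updated.
- A reader might infer that every input is on file at every visit, so that a continuous score repairs all three time points. Cholesterol is missing at T2, so it repairs T0 and T3 only.

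Finally, holding age at T0 replaces the participant's actual risk at T3 with a hypothetical one. That is a fair reason to leave it optional.

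**Conclusion.** The concern holds as a matter of precision. If chart cells are analysed as the outcome section is written, the comparisons of B, C and D with A remain unbiased but become less precise. In the assumed scenarios, power falls from 84–90% with a continuous score to 70–72% with banding and age fixed, and to 48–63% with banding and age advancing. These values depend on assumed bands, coefficients and effects. They come from a simple comparison of mean changes, not from the planned mixed model, and they are not an estimate of this trial's power. Once the score is continuous, the treatment of age matters almost only for the within-arm change from baseline.

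Separately, the planned T2 risk does not fit the article's own blood sampling schedule. That conflict is firmer than the banding point, because it needs no assumption about the charts.

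**What to change.** - State that, for the outcome analysis, SCORE 2 is computed as a continuous value at T0 and T3 from the recorded age, sex, systolic pressure, total and HDL cholesterol and smoking status, and cite the equation used. Keep the charts for eligibility and for explaining risk to participants.
- Optionally, hold age at its T0 value in the T3 calculation, or state that only between-arm contrasts will be interpreted.
- Reconcile the T2 risk in the Cardiovascular risk change section with the Study procedure and Lipid profile sections: remove it, or say which cholesterol value it uses and where that value comes from. If it is removed, the model for this outcome has a single follow-up visit.

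The cost is a sentence or two and a short piece of code for T0 and T3, where the inputs are planned to be collected. The downside is that the analysed value may differ slightly from the one shown to the participant.

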#### Lipid profile

Blood analysis will be conducted at T0 and T3 to measure changes in lipid levels compared to baseline. Parameters examined will include total cholesterol, HDL and LDL cholesterol, and triglycerides.

By assessing these measures at different time points throughout the trial, the study will evaluate the impact and progress achieved by participants over the course of the intervention.

### Data collection and management

The study data will be collected and managed using the REDCap electronic data capture tools (27). Access to the REDCap web platform and data entry/management will be restricted to individuals officially registered as study investigators or data managers. They will receive user login credentials to ensure secure access to the system. Each study unit will enter the data into the eCRFs in a pseudonymized form, following established protocols and within the designated timeframes after each participant visit.

### Statistical methods

#### Sample size estimation

Based on a conservative assumption, considering that this is the first study in this context, we anticipate that 15% of participants in group D will transition from unfavorable to intermediate lifestyle patterns during the follow-up period, compared to 10% in group C, 8% in group B, and 5% in group A. To achieve a statistical power of at least 80% with a significance level of 0.05, while accounting for a potential withdrawal rate of 30%, a total of 1,020 participants will need to be recruited, with 255 participants in each group. This sample size allows us to have a statistical power >80% to detect a difference of 5 mg/dL in LDL cholesterol (our secondary outcome) with a standard deviation of 15 mg/dL and a significance level of 0.05%, as tested in previous studies (28). An interim analysis will be conducted when 50% of the participants will be recruited to assess whether the sample size remains adequate for detecting the anticipated differences in lifestyle patterns and LDL cholesterol levels.

#### Statistical methods for primary and secondary outcomes

The primary analysis will be based on the intention-to-treat principle, where all randomized participants will be analyzed according to their allocated study arm. Baseline characteristics of the four arms will be summarized using descriptive statistics. The baseline characteristics of those who withdraw will be assessed against those who remain in the study.

Groups D, C, and B will be compared with group A to evaluate the marginal effect of adding at least one intervention or both. The analysis will employ adjusted mixed-effect models for repeated measures to assess significant differences in lifestyle patterns, lipid, and CVD risk profiles from baseline to the various follow-up time points (T).

Furthermore, an analysis of the primary outcome will be conducted in a per-protocol fashion to account for non-compliance with uptake of the CVD PRS or use of the app/smart band evaluated at T2 and T3, as well as missed appointments for the complete CVD risk result, as prescribed by their allocated intervention.

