## Objectives

We will evaluate whether the use of innovative technologies to gather information on lifestyle and genetic determinants in the primary prevention setting can lead to changes in individuals' behaviors and CVD risk. The primary objective is to assess the efficacy of providing CVD polygenic risk score (CVD PRS) information, measured at baseline, either alone or in combination with the use of an app and a smart band (digital technology), on two endpoints: (i) changes in lifestyle patterns, and (ii) modification in CVD risk profiles. The potential lifestyle modification will also be evaluated in relation to other factors such as psychological status, knowledge and attitudes toward CVDs and personalized medicine, and acceptance of wearable devices, which can influence citizens' behavior.

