### Hypothesis

The hypothesis is that achieving the endpoints is more likely with at least one of these interventions (CVD PRS alone or in combination with digital technology) compared to individuals who only undergo the traditional CVD risk assessment at the beginning of the study, as well as compared to individuals who receive traditional risk assessment along with the use of smart band.

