## Study design

This is an RCT with four parallel arms, as illustrated in Figure 1. Participants will be randomly assigned to the following intervention groups:

A. No Intervention—Traditional CVD risk assessment.B. Traditional CVD risk assessment plus Genetic testing (CVD PRS).C. Traditional CVD risk assessment plus Digital intervention (use of an app and a smart band).D. Traditional CVD risk assessment plus Digital intervention (use of an app and a smart band) plus genetic testing (CVD PRS).

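### The hypothesis sets the PRS arms against the smart-band arm C as well as A, but the analysis names only comparisons with A, so PRS added to digital (D vs C) has no planned contrast

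*Protocol article*

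**What the plan says.** The Objectives section makes PRS information the subject of the primary objective, to be evaluated "either alone or in combination with the use of an app and a smart band (digital technology), on two endpoints".

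The Hypothesis section says the endpoints are more likely with at least one PRS intervention, alone or with digital technology, and names two comparators. The first is arm A: "compared to individuals who only undergo the traditional CVD risk assessment at the beginning of the study". The second is arm C: "as well as compared to individuals who receive traditional risk assessment along with the use of smart band".

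The Study design section defines arm D as "Traditional CVD risk assessment plus Digital intervention (use of an app and a smart band) plus genetic testing (CVD PRS"). D therefore differs from C by PRS only, and from A by PRS and digital together.

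The section on statistical methods for primary and secondary outcomes lists the comparisons: "Groups D, C, and B will be compared with group A to evaluate the marginal effect of adding at least one intervention or both". The model is an adjusted mixed-effect model for repeated measures.

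The sample size section assumes that "15% of participants in group D will transition from unfavorable to intermediate lifestyle patterns during the follow-up period". For the other arms it sets rates of 5% (A), 8% (B) and 10% (C).

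**The concern.** The list of comparisons does not cover the stated hypothesis. Half of the hypothesis is a claim against arm C, and no comparison with C is named in which a PRS arm takes part. The listed contrasts are B vs A (PRS alone), C vs A (digital alone) and D vs A (both). D vs C, which shows what PRS adds for people who already have the app and band, is absent, although both arms are randomised.

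At stake is what the trial can say about its primary objective. Of the three named contrasts, only D vs A has more than 80% power on the planning rates, and it cannot separate PRS from digital. The Discussion itself reports that earlier data consistently found no significant effect of genetic feedback, so this separation matters. A contrast chosen from the fitted model after the results are known would not carry the weight of a pre-specified one.

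**Working it through.** **Sections side by side**

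| Contrast | What differs | Needed by the Hypothesis | Named in the analysis |
|---|---|---|---|
| B vs A | PRS, without digital | yes (vs A) | yes |
| D vs A | PRS and digital together | yes (vs A) | yes |
| C vs A | digital only | no | yes |
| D vs C | PRS, on top of digital | yes (vs C) | no |
| B vs C | PRS in place of digital | possible route (vs C) | no |

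The hypothesis needs at least one of B and D to beat C. On the planning rates D is the arm that does so (15% vs 10%), so D vs C carries that half of the hypothesis.

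**Inputs (sample size section).** Rates A 5%, B 8%, C 10%, D 15%; 255 per arm; 30% withdrawal; alpha 0.05. Sidedness is not stated, and I take two-sided. Evaluable per arm: 255 × 0.7 = 178.5, taken as 178.

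**The plan's own figure.** The 1,020 is close to what a global four-group chi-square test (3 df) gives. The mean rate is 9.5% and the sum of squared deviations is 0.0053, so the noncentrality per participant per arm is 0.0053 / (0.095 × 0.905) = 0.0616. Power of 80% needs 177 per arm; 177 / 0.7 = 252.9, or 253 per arm and 1,012 in total. At 178 per arm the global power is 80.3%. No pairwise contrast at two-sided 0.05 gives 255: D vs A needs 202 per arm after withdrawal, C vs A 622, B vs A 1,513 and D vs C 980. The protocol does not name the test behind its figure, so the global test is an inference.

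**Composition of D vs A on the planning rates**

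- D − A = 15 − 5 = 10 points.
- Through C: digital alone 10 − 5 = 5, then PRS on top of digital 15 − 10 = 5.
- Through B: PRS alone 8 − 5 = 3, then digital on top of PRS 15 − 8 = 7.

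The split depends on the path. The 5 points in D vs C are the effect of PRS added to digital, not a unique PRS share of D vs A.

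**Pairwise power.** Power = Φ[(|p1 − p2| − 1.96·s0) / s1], with s0 = √(2·p̄(1 − p̄)/n) and s1 = √([p1(1 − p1) + p2(1 − p2)]/n); the opposite tail adds at most 0.1 point to the rows for 178 per arm.

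For D vs C at n = 178: s0 = 0.03506, s1 = 0.03496, (0.05 − 1.96 × 0.03506) / 0.03496 = −0.535, power 0.296.

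| Contrast | Rates | n per side | Power |
|---|---|---|---|
| D vs A | 15% vs 5% | 178 | 88.5% |
| C vs A | 10% vs 5% | 178 | 43.3% |
| D vs C | 15% vs 10% | 178 | about 30% |
| B vs A | 8% vs 5% | 178 | about 21% |
| B+D vs A+C | 11.5% vs 7.5% | 357 | about 45% |

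With all 255 per arm evaluable, D vs C has 40.0%. For 80% it needs 686 evaluable per arm, or 686 / 0.7 = 980 recruited per arm.

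**If PRS adds nothing to digital.** D's true rate then equals C's, 10%. D vs A becomes 10% vs 5%, the C vs A row: significant about 43% of the time at 178 per arm.

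**The case against.** The strongest reply is that the list of comparisons does not exclude others. A four-arm mixed model can yield D vs C, and this is a condensed article whose analysis plan is not shown. That is fair as far as it goes: one cannot say that D vs C will never be examined. But the article does not leave the comparisons open. It lists them and states their purpose, and the list does not match its own Hypothesis section. That mismatch stands whatever another document adds.

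A reader might draw three stronger conclusions, and the text does not support them:

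- *That PRS goes untested.* B vs A is planned and isolates PRS without digital.
- *That the planning rates contradict the hypothesis, because B (8%) is assumed below C (10%).* The hypothesis asks for at least one PRS intervention to do better. D at 15% against C at 10% satisfies that, so the Hypothesis section needs no rewording on this ground.
- *That D vs A will be presented as a PRS effect.* No section says so. The analysis section describes adding one intervention or both, and D vs A is a legitimate estimate for the combined package. C vs A is also useful, because it gives the digital effect needed to read D vs A.

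It is also true that adding D vs C aligns the text without supplying power. This limits what the fix achieves but does not remove the inconsistency.

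**Conclusion.** The concern holds as an inconsistency between the Hypothesis section and the list of comparisons. The hypothesis against arm C has no named analysis, and the effect of PRS added to digital has no named contrast. D vs A cannot stand in for it: on the planning rates C vs A alone equals 5 of its 10 points, and with no added PRS effect it would still be significant about 43% of the time.

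The power figures rest on the planning rates applied to all evaluable participants, 178 per arm, two-sided 0.05, simple two-proportion tests and no multiplicity adjustment. The planned repeated-measures model could shift them somewhat. The inconsistency itself does not depend on them.

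**What to change.** In the section on statistical methods for primary and secondary outcomes:

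1. Pre-specify D vs C, from the same mixed model, as the contrast for the second half of the hypothesis.
2. Keep B vs A and label it the PRS-alone contrast.
3. State that D vs A estimates the effect of the combined package, not of PRS.
4. Optionally, add the pooled PRS effect (B+D vs A+C) as a supportive estimate. It assumes little PRS × digital interaction. The planning rates put the PRS effect at 3 points without digital and 5 with it, and the pooled 4 points (11.5 − 7.5) average the two.

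The cost is one more contrast in the multiplicity scheme; no further participants, visits or data are needed. The protocol should say openly that on its own rates D vs C has about 30% power at 178 evaluable per arm, and the pooled contrast about 45%. A non-significant D vs C should then be read through its confidence interval and not as evidence that PRS adds nothing.
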